## Abstract

**Background:**

Type 2 diabetes (diabetes) is a serious threat to public health in the United States and disproportionally affects many racial/ethnic minority groups, including African Americans. Limited access to treatment and high attrition rates further contribute to health disparities in diabetes-related morbidity and mortality among minorities. Greater opportunities for increasing access and decreasing barriers to treatment are needed. Technology-based interventions have potential for accomplishing this goal but evidence of feasibility and potential effectiveness is lacking, especially for populations that traditionally have limited educational attainment and low computer literacy.

**Objective:**

This paper describes the design and methods of a pilot randomized clinical trial that will compare the feasibility and potential efficacy of delivering a diabetes self-management intervention via a virtual world vs. a face-to-face format.

**Methods:**

Study participants (n=100) will be African American women with uncontrolled type 2 diabetes recruited from primary care practices and affiliated health centers at a large safety net hospital in Massachusetts. Participants will be randomized into a virtual world-based (VW) intervention condition or a face-to-face control condition. Both conditions provide the same theory-based curriculum and equivalent exposure to the self-management program (eight group sessions), and both will be delivered by a single intervention team (a dietitian and a diabetes educator). Assessments will be conducted at baseline and 4 months. Feasibility will be determined by evaluating the degree to which participants engage in the VW-based intervention compared to face to face (number of sessions completed). Potential efficacy will be determined by comparing change in physiological (glycemic control) and behavioral (self-reported dietary intake, physical activity, blood glucose self-monitoring, and medication adherence) outcomes between the experimental and control groups.

**Results:**

The primary outcomes of interest are feasibility of the VW intervention and its potential efficacy on glucose control and diabetes self-management behaviors, compared to the face-to-face condition. Analysis will use a two-sample Kolmogorov-Smirnov test for changes in variable distribution. *P* values will be calculated using binomial tests for proportions and *t* tests for continuous variables.

**Conclusions:**

If the intervention is found to be feasible and promising, it will be tested in a larger RCT.

## Introduction

Type 2 diabetes (diabetes) is a serious threat to public health in the United States and the world and is a costly disease at the individual and societal levels. In the United States, its prevalence has risen among all ethnic groups, especially among certain racial/ethnic minority groups such as African-Americans who have had a near doubling of prevalence (now 13%) since 1988 [1,2]. Diabetes has numerous and serious health risks associated with poor control [2]. Expert guidelines promote counseling for patient health behavior change targeting increased physical activity, reduction in caloric intake and weight, and promotion of adherence to medication [3]. Among individuals with diabetes, women and African Americans report the lowest levels of physical activity and more than half (66%) of African Americans with diabetes report high-fat diets [4,5]. Although self-management programs have proven efficacy, attrition rates are high [6]. Factors reported as contributing to attrition include competing family responsibilities, conflict with program hours, and distance to services [7]. Web-based methods to improve diabetes outcomes could improve access to behavior counseling and have shown promise in improving health behaviors and glycemic control [8]. However, the feasibility of intervening through web-based methods has been questioned due to a real or perceived digital divide or socioeconomic inequalities among individuals in access to information technologies. For example, only 49% of African Americans compared to 68% of Caucasians have a broadband Internet connection at home [9]. In addition to this divide in access to connectivity and hardware, researchers have identified a skill and knowledge divide on the basis of technological competency and digital literacy [10].

Virtual world (VW) environments are potentially suitable environments for supporting patient education delivery, including diabetes self-management programming. VWs are 3D, immersive, online places where people enter and participate as an avatar. Once in the VW, participant avatars can walk, run, fly, talk, travel, and interact with the other people or structures present in the virtual space. The rich visual landscape, in combination with the mediated presence via avatar, gives the participant a strong sense of “being there”. VWs offer vast opportunities for interaction, intense engagement, and opportunities for scripted immersive experiences, simulations, role-playing, and constructivist learning. Sense of presence, easy access, and anonymity afforded by the avatar may lead to greater interaction and group cohesiveness, as well as engagement and attention, compared to other web-based approaches [11,12]. Currently there are over 300 such online VWs, such as Jibe, OpenSim, Spoton3D, Open Wonderland, and Second Life (SL). Created and maintained by companies, universities, or individuals, some of these online environments are free of charge or some assess monthly or per-use fees. Although the use of VWs has been shown to influence behavior in the “real” world [13], studies are limited and have not targeted the spectrum of diabetes self-management behaviors.

The objective of this paper is to describe the design and methods of a pilot study that will compare the feasibility and potential efficacy of delivering a diabetes self-management intervention via a VW (delivered in Second Life, or SL) versus a face-to-face format.

## Methods

### Design

Women in Control is a pilot randomized clinical trial funded by the National Library of Medicine/National Institutes of Health that will evaluate the feasibility and potential efficacy of a diabetes self-management intervention delivered through interactive sessions within a Virtual World (VW), compared to a face-to-face format, to improve glucose control and enhance adherence to diabetes self-management behaviors in a population of African American women.

### Hypothesis

We hypothesize that the VW-based experimental intervention condition will produce outcomes related to feasibility and potential efficacy that are comparable or greater than those observed in the face-to-face control condition.

### Interventions

The intervention content will be adapted from the CDC/NIH program “Power to Prevent” (P2P) [14], a culturally appropriate, evidence-based behavior-change curriculum designed for face-to-face delivery to African American patients with diabetes or pre-diabetes. The intervention approach is theory-based [15] and thus seeks to enhance diabetes knowledge, optimize attitudes toward diabetes self-management (ie, self-efficacy, outcome expectations), and develop behavioral self-management skills (eg, goal setting, tracking self-management behaviors and glucose levels, problem-solving) to facilitate changes in dietary intake, physical activity, blood glucose self-monitoring, and medication adherence. Curriculum objectives and topics are summarized in Table 1.

**Table 1 table1:** Women in Control diabetes self-management program outline.

Session number	Session topics
1. (Individual)	Intake session—Program overview; Review of informational handouts; Take history of dietary and physical activity habits, medication intake, blood glucose self-monitoring; Discuss action plan and tracking; Set initial goal
2. (Group)	Getting Started—Welcome and introductions; What is diabetes; Diabetes self-management goals; Achieving control through small steps; Ways to increase physical activity
3. (Group)	Decreasing Your Hunger—Food and blood glucose; Healthy food choices from three food groups; Healthy fats; Fiber
4. (Group)	Using Food Labels to Track Carbs and Fat—Finding carbohydrates and fat grams in a food label; Healthy amounts of fiber per serving; Decreasing fat grams in food choices; Substituting healthful foods for less healthful foods
5. (Group)	What Have We Learned So Far?—Review of the effects of physical activity and food on blood sugar
6. (Group)	Diabetes Medications—Benefit of medications in diabetes management; How medications work; Importance of adhering to the medication regimen; Strategies to enhance medication adherence
7. (Group)	Physical Activity for You and Your Family—Review of overall benefits of physical activity for patient and family; Eliciting support for physical activity from others; Relapse prevention
8. (Group)	Managing Food Intake and Blood Sugar Outside of the Home—Understanding the difference between portion size and serving size; Strategies to improve food choices when eating out; Preventing overeating when eating out
9. (Group)	Empowering Yourself—Asking questions of health care providers; Remembering goal levels for A1c, blood pressure, and cholesterol; Graduation

We will deliver this curriculum through a series of weekly sessions that begin with an individual intake session, followed by 8 weekly sessions. Sessions will be delivered in either a VW or face-to-face environment in groups of approximately 12-15 participants by a single intervention team (a dietitian and a diabetes educator) for the same duration (90-minute sessions) using the same protocol and materials for both conditions. Participants in both conditions will receive 2 sessions of computer training and will be provided with an Internet-enabled laptop computer upon training completion. Multimedia Appendix 1 summarizes the specific activities conducted during each computer training.

The face-to-face group sessions will take place in a large conference room at Boston Medical Center. All face-to-face participants will receive transportation vouchers to facilitate attendance. VW-based sessions will take place in an open-air VW forum built especially for the intervention with adequate structures and required visuals/displays (see Figures 1 to 4). Although the VW sessions will last 90 minutes, these participants will be asked to log in 30 minutes prior to each session in order to test their sound and troubleshoot any connection problems. To facilitate session flow, a triage system will assign participants to “producers” (technical support staff) as technology needs arise. As in the face-to-face condition, both interventionists will attend every group session (alternating facilitation). In the VW condition, the non-leading interventionist will take notes in the local chat and provide general back-up, while in the face-to-face condition, the non-leading interventionist will provide logistical assistance. Multimedia Appendix 1 compares similarities and differences of intervention implementation among these conditions in greater detail.

Two members of the research team will oversee fidelity of intervention content and style for both conditions via direct observation and review of recorded sessions. Interventionists will be provided with feedback on errors of omission and commission, and additional support will be given on an ongoing basis as needed.

**Figure 1 figure1:**
[figure not shown]
Virtual world forum.

**Figure 2 figure2:**
[figure not shown]
Floor pattern: self-efficacy ruler.

**Figure 3 figure3:**
[figure not shown]
Club one island.

**Figure 4 figure4:**
[figure not shown]
Dancing stage.

### Randomization

Upon completion of all study assessments, we will randomize participants to either the VW-based experimental intervention condition or the face-to-face control condition. A block randomization scheme with a block size of 4, developed by StudyTRAX software (v3.0.0103), will be used. Randomization will be stratified on age and hemoglobin A1c measured at baseline. Participants will be informed about their randomization assignment via phone.

### Outcomes and Study Measures

The primary outcomes of interest are feasibility of the VW intervention and its potential efficacy compared to the face-to-face condition. Feasibility will be determined by evaluating the degree to which participants engage in the VW-based intervention compared to face-to-face (number of sessions completed). Potential efficacy will be determined by comparing change in glucose control and self-management behaviors between the experimental and control groups, from baseline to the 4-month follow-up.

Assessments will be performed at baseline and at 4-month follow-up. HbA1c tests will be used to assess average blood glucose level over the previous 2-3 months. Non-fasting venous blood samples from an antecubital vein will be collected after the subject remains seated for 10 minutes, in accordance with standard research protocols [16]. Boston Medical Center laboratories will analyze the specimens. At each time point, dietary intake will be assessed by two unannounced 24-hr dietary recalls (24HRs) [17] administered on randomly selected days (60% probability of a weekday and 40% probability of a weekend day). 24HRs are well suited for the characteristics of the target population (ie, language, illiteracy/low educational level, ethnic foods) that limit use of other/additional assessment methods. Also at each time point, 24-hour physical activity recalls will be administered immediately after the 24-hr dietary recalls [18], followed by recalls of blood glucose self-monitoring and medication adherence. Other measures will include blood pressure [19], cholesterol, body mass index, waist and hip circumference, depressive symptoms [20,21], self-efficacy for diabetes management [22], health literacy [23], social support [24,25], perceived stress [26], and quality of life [27]. Demographic factors, smoking history, alcohol intake, current use of prescription and non-prescription medications, as well as use of home remedies, and experience with computers and the Internet will be assessed via survey. We will assess patient satisfaction at the 4-month follow-up. Intervention implementation costs (costs that would be incurred if the intervention were to be implemented outside the context of the research project) will be tracked.

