### Quantitative Evaluation: Analytic Plan

#### Sample Size and Power Calculations

As a comparative effectiveness study, patients in both arms will receive interventions potentially resulting in improvements in the primary outcomes. Hence, a very large sample size would be required to demonstrate either statistically significant comparative effectiveness or superiority of one group over the other. As a result, and in recognition of the project’s status as a feasibility study, the study was powered to be able to demonstrate within group improvements in one of the key outcomes: physical activity. A sample size of 47 was determined to be sufficient to show a within group improvement, from pre- to post-, of 20% of the sample from inactive to moderate intensity physical activity, with a power of 80% at 0.05% level of significance.

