#### Analysis and Statistical Tests

Our null hypothesis is that there will be no significant differences in outcome measures between the VW and face-to-face conditions. We will test this null hypothesis against the alternative that the VW condition is not as effective as face-to-face intervention using a two-sample Kolmogorov-Smirnov test for changes distributions of A1c. In other words, the VW intervention will be as good as or better than face-to-face intervention in decreasing A1c. The *P* values will be calculated using binomial tests for proportions and *t* tests for continuous variables. We will use RStudio (version 0.96.330) [28] for statistical analysis.

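### Potential efficacy is defined only relative to a face-to-face arm given the same curriculum, so the A1c comparison cannot separate two formats that work equally well from two that do not work

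*Protocol article*

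**What the plan says.** All references are to the Protocol article.

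- **Definition.** Outcomes and Study Measures: "Potential efficacy will be determined by comparing change in glucose control and self-management behaviors between the experimental and control groups", from baseline to 4 months. The Abstract (Methods) says the same and lists glycemic control plus four behaviours: diet, physical activity, glucose self-monitoring and medication adherence.
- **Success pattern.** Hypothesis: the VW arm is expected to give results "comparable or greater than those observed in the face-to-face control condition".
- **Test.** Analysis and Statistical Tests: "Our null hypothesis is that there will be no significant differences in outcome measures between the VW and face-to-face conditions". This is set against "the alternative that the VW condition is not as effective as face-to-face intervention using a two-sample Kolmogorov-Smirnov test" applied to A1c changes, and the favourable result is restated as "the VW intervention will be as good as or better than face-to-face intervention in decreasing A1c". No margin and no significance level is given for this test.
- **Sample size.** Sample Size and Power Calculations says that "patients in both arms will receive interventions potentially resulting in improvements in the primary outcomes", that a between-arm conclusion would need a very large sample, and that the study is therefore powered (47 women) on within-group improvement in physical activity.
- **Next step.** Abstract, Conclusions: "If the intervention is found to be feasible and promising, it will be tested in a larger RCT".
- **Arms.** Both get the same curriculum, exposure, intervention team, computer training and laptop. No arm is untreated.

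**The concern.** The A1c judgement has one input, VW change minus face-to-face change. Two arms that share a curriculum may well move together, and they do so whether both improve, both stay flat or both get worse. Equality with face-to-face says something about efficacy only if face-to-face lowered A1c in these women, and the stated definition contains no check of that.

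The sample size section adds a mismatch. It gives up the between-arm question as out of reach and sizes the study for a within-group question, yet the outcome definition and the test section base the efficacy conclusion on the between-arm comparison. A programme with no effect on glucose control in either format could then be reported as showing potential efficacy, and that report would feed the case for a larger trial.

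**Working it through.** **1. The plan's own figure.** The stated 47 is for a within-group gain of d = 0.20, with 80% power. The paired (McNemar) formula is n = [z_a·√p + z_b·√(p − d²)]² / d², where p is the proportion who change in either direction. At two-sided 5% (z_a = 1.960, z_b = 0.842):
- 22.5% improving and 2.5% worsening, p = 0.25: n = 46.6, so 47.
- Nobody worsening, p = 0.20: n = 36.8, so 37.

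A one-sample test of 0.5 against 0.7 also gives 47. The figure therefore reproduces at 5%, with inputs that the article does not state. At the printed level of 0.05% the paired formula needs at least 82 (one-sided) or 90 (two-sided), so 0.05% looks like a slip for 5%. The calculation concerns physical activity within an arm and says nothing about the A1c comparison.

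**2. The A1c comparison does not respond to absolute change.** Let F and G be the distributions of A1c change in the two arms. The K-S statistic is the largest gap between F(x) and G(x). If every woman in both arms shifts by the same amount c, the gap between F(x − c) and G(x − c) is unchanged. The t statistic for the difference is also unchanged. A common fall, no change and a common rise all give the same pass rate.

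**3. Pass rate when neither arm changes.** Assumptions: 5% level, continuous A1c changes, equal arms of 40, 47 or 50 (100 women in blocks of 4 suggest about 50 per arm; the lower values allow for loss). For the one-sided exact K-S test with n per arm, P(D⁺ ≥ k/n) = C(2n, n − k) / C(2n, n). The smallest k that rejects is 11, 12 and 13 for n = 40, 47 and 50. The two-sided exact test rejects from k = 13, 14 and 14.

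| n per arm | one-sided K-S not rejected | two-sided K-S not rejected |
|---|---|---|
| 40 | 95.1% | 97.1% |
| 47 | 95.3% | 97.0% |
| 50 | 96.6% | 96.1% |

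A one-sided t test gives 95%. None of these depends on the SD. With A1c rounded to 0.1, the one-sided K-S figure is 96-98%.

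**4. If all five outcomes had to be non-rejected.** With independent outcomes, 0.95⁵ = 77%. With correlation 0.3 it is 81%, and with correlation 0.6 it is 85%.

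**5. How much comes from the missing margin.** Assume an SD of A1c change of 1.5 points and 47 per arm, so SE = 1.5 × √(2/47) = 0.309. With no true difference, a one-sided 2.5% non-inferiority test passes in 16%, 25% and 36% of trials for assumed margins of 0.3, 0.4 and 0.5 points. Over SDs of 1.2 to 1.8 the range is 12-52%. The article gives neither an SD nor a margin.

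**6. What absolute change adds.** If VW must also show a fall (upper 95% limit below 0), the pass rate with no change in either arm drops to about 2-3%. The same requirement is met in only about 60% of trials when the true fall is 0.5 points (SD 1.5, 47 women).

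**The case against.** **A reader might infer that VW would be called promising 95% of the time when nothing works.** The documents do not support that. The word promising has no definition, it is joined to feasibility, efficacy also covers four behaviours, and no level is stated for the between-arm test. The 95-97% is the pass rate of one A1c test at an assumed 5%.

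**Much of that figure reflects reading non-rejection as equality.** This stands: step 5 shows 16-36% once a margin of 0.3 to 0.5 is assumed at SD 1.5. The separate point survives, because a test with a margin is just as blind to whether either arm improved.

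**The plan does include an absolute improvement.** Also true: the study is sized for a within-group gain in physical activity, and the t and binomial tests are not restricted to between-arm use. So it would be wrong to say that no absolute change is planned. What is missing is any link from that result to the efficacy conclusion, and any within-arm criterion for A1c.

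**The comparator has prior support.** The Introduction says self-management programmes have proven efficacy, and the Interventions section calls the source curriculum evidence-based and meant for face-to-face use. Active-control designs commonly rest on such evidence. But the curriculum is adapted here, the article itself says only that improvement is possible, and the definition includes no check that it occurred.

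**A within-arm fall is uncontrolled.** This stands. Secular change, treatment changes by usual providers and regression to the mean after selection on HbA1c above 8 could all produce one. A hard significance requirement would also miss about 40% of true 0.5-point falls, so it is not proposed.

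**The analysis plan may deal with this.** The point concerns the definition that the article itself states, not detail left to another document.

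**Conclusion.** The concern holds in this form: the stated definition of potential efficacy is relative only, and it does not fit a sample size section that sets the between-arm question aside in favour of a within-group one. Followed as written, the A1c comparison is passed about 95-97% of the time when neither arm improves, and equally often when both worsen by the same amount. That figure rests on a 5% level, the A1c test alone and equal arms of 40 to 50. It falls to 77-85% if A1c and all four behaviours must be non-rejected. It is not the probability of proceeding to a larger trial, which cannot be computed from the article.

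The consequence is moderate. The next step is another randomised trial, and the Discussion admits that the pilot is too small for a comparative conclusion. The plan should still be changed, because the correction is cheap and alters what the trial can say.

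**What to change.** Reconcile Outcomes and Study Measures, Sample Size and Power Calculations, and Analysis and Statistical Tests, and bring the Hypothesis into line:

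1. Add to the definition of potential efficacy the mean A1c change from the measured baseline sample (not the qualifying chart value) to 4 months, with its 95% CI, for VW and for face-to-face.
2. State how the powered within-group physical activity result enters the efficacy conclusion.
3. Report the between-arm difference in A1c change with a 95% CI, and stop reading a non-rejected test as showing that VW is as good.
4. State that if the arms show no fall in A1c, comparability will not be read as evidence of efficacy, and that a within-arm fall is supportive only, because it is uncontrolled.

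**Cost.** Some rewording, two within-arm estimates and one interval from A1c values already collected; no extra patients or visits. The conclusion will be more cautious. With the assumed SD of 1.5 and 47 per arm, the 95% CI half-width is about 2.01 × 1.5/√47 = 0.44 points within an arm and 1.99 × 0.309 = 0.61 between arms.

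### Recall days are not matched between baseline and 4 months, which adds modest, avoidable noise to change in diet and physical activity

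*Protocol article*

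**What the plan says.** All of this is in the protocol article, mainly under Outcomes and Study Measures.

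- There are two visits: "Assessments will be performed at baseline and at 4-month follow-up".
- There are two recalls per visit: "At each time point, dietary intake will be assessed by two unannounced 24-hr dietary recalls (24HRs". They are "administered on randomly selected days (60% probability of a weekday and 40% probability of a weekend day".
- Activity is taken at the same contacts: "24-hour physical activity recalls will be administered immediately after the 24-hr dietary recalls". Glucose self-monitoring and medication adherence are then recalled, with no recall window stated for either.
- Potential efficacy is judged by "comparing change in glucose control and self-management behaviors between the experimental and control groups, from baseline to the 4-month follow-up".
- Under Sample Size and Power Calculations, "the study was powered to be able to demonstrate within group improvements in one of the key outcomes: physical activity".

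The article states a probability for each day. It states no quota of one weekday and one weekend day, no matching of the mix across visits, and no use of day type in the analysis.

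**The concern.** Eating and activity commonly differ between weekdays and weekends. With only two days per visit, the number of weekend days is a coarse random quantity: 0, 1 or 2. When it differs between a woman's two visits, part of her measured change reflects which days were drawn.

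The same contacts supply diet and physical activity, so one scheduling rule affects both. What is at stake is precision in a 100-woman pilot, including for the within-group activity outcome on which the sample size rests. HbA1c and session attendance, which do not come from recalls, are untouched.

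**Working it through.** The 60/40 split is a design input, so there is no derived figure of the plan to reproduce. The sample size of 47 is not used below.

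**Inputs.** From the article: p = 0.40 per day for a weekend, two days per visit, two visits. Not in the article: D, the weekend-weekday difference, and s, the day-to-day SD within a day type. Both are kept as symbols, and any values given to them are assumptions. Day-to-day errors are taken as independent.

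**1. Mix at one visit, independent draws.** Weekend days follow Bin(2, 0.4):
- none: 0.6² = 0.36
- one: 2 × 0.4 × 0.6 = 0.48
- two: 0.4² = 0.16

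**2. Mismatch between visits.** P(same) = 0.36² + 0.48² + 0.16² = 0.1296 + 0.2304 + 0.0256 = 0.3856, so P(different) = 61.4%. Within that, 2 × 0.36 × 0.16 = 11.5% of women have two weekdays at one visit and two weekend days at the other.

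**3. If the two days of a pair are dependent.** Keep the 0.4 marginal and let a = P(both weekend), with visits still independent. Then P(different) = 1 − [a² + (0.8 − 2a)² + (0.2 + a)²].
- a = 0 (two weekend days never allowed): 32.0%
- a = 0.16 (independence): 61.4%
- a = 0.233 (the maximum): 64.7%
- a = 0.4 (both days always of the same type): 48.0%

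If the mix were matched across visits, the figure would be 0%.

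**4. Variance of a change score.** The weekend fraction at a visit has variance 0.4 × 0.6 / 2 = 0.12, so its change has variance 0.24 (SD 0.49).
- Current rule, unweighted mean of two days: s²/2 + s²/2 + 0.24·D² = s² + 0.24·D².
- Same mix at both visits, unweighted mean: s².

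**5. Size, on assumed values only.** Take D = 200 kcal, so 0.24·D² = 9,600.
- s = 300: √(90,000 + 9,600) = 316 against 300, or 5.2% larger
- s = 500: √(250,000 + 9,600) = 510 against 500, or 1.9% larger
- s = 700: √(490,000 + 9,600) = 707 against 700, or 1.0% larger

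True between-woman variation in change would shrink these percentages further.

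**6. Would weighting to a 7-day week help?** With one weekday and one weekend day, weights 5/7 and 2/7 give a variance per visit of (25 + 4)/49 · s² = 0.592·s², so change has variance 1.184·s². That beats the current rule only if 0.24·D² > 0.184·s², that is, D > 0.875·s. It is always worse than the s² of the matched, unweighted mean.

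**7. Would correcting the 40% help?** The calendar weekend share is 2/7 = 28.6% if the weekend is Saturday and Sunday. Independent draws at 2/7 give P(same) = (25/49)² + (20/49)² + (4/49)² = 0.434, so 56.6% of women would still be mismatched.

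**The case against.** The strongest reply is that nothing here is an error. The same 60/40 rule governs both arms and both visits, so the expected weekend share is 40% everywhere and cancels from mean change and from the arm comparison. Independence is not written. An article may leave the scheduling algorithm and any day-type adjustment to a fuller document. A 40% weekend draw is also defensible: at 2/7, 51% of women ((5/7)² = 25/49) would have no weekend day at a visit, against 36% at 40%. And a mismatch count is not an effect size.

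Most of this stands, and it limits the point to precision. What remains is that the article does state a per-day probability rule, and on its natural reading that rule leaves the mix to chance at each visit, when holding it constant would cost almost nothing. If a fuller document matches the mix, the point falls away.

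A reader might infer more, and the documents do not support it:
- **That the treatment comparison is biased.** It is not, for the reason above.
- **That weekend over-representation distorts the results.** It shifts absolute levels, not change, provided the intervention effect is similar on both day types. If Friday counts as weekend, the calendar share is 3/7 = 42.9% and there is no over-representation.
- **That all four behaviours are affected.** Only diet and activity are described as 24-hour recalls. For self-monitoring and adherence, it depends on a recall window that is not given.
- **That women will flip between inactive and moderate, with a known power loss.** The article does not say how two recalls become an activity category, so neither can be calculated.

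**Conclusion.** The point holds as a cheap improvement in precision. Under independent draws, 61.4% of women will have a different weekend-day count at the two visits (about 32% to 65% if days within a pair are dependent), and the variance of change in diet and physical activity rises by 0.24·D². Neither D nor s is in the article. On plausible but assumed diet values, the SD of change rises by low single-digit percentages. The noise reaches physical activity, the outcome in the sample-size statement, by an amount the article does not allow to be quantified. The conclusion rests on reading the per-day probability as independent draws, with no matching across visits.

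**What to change.** Give each woman the same day-type mix at both visits, for example one weekday and one weekend day each time, with the specific day still random and unannounced. Analyse change with the unweighted mean of the two days.

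If the 60/40 draw is kept, include each woman's weekend-day count at each visit, or its change, as a covariate in the change analysis.

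Do not apply 5/7 and 2/7 weights to the change analysis, for the reason in step 6 of the working. Keep them for descriptive estimates of usual intake or activity.

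Cost: the same number of recalls, a small change to the call schedule, and slightly less scheduling freedom. With one day of each type the unweighted level is 50% weekend, further from 2/7 than the present 40%, so unweighted levels should not be reported as usual intake or activity.
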